***Research Plan.***

*1. Subjects.* N = 80 healthy males and females 65 - 85 y. *2. Design/Intervention.* Randomized, double-blind study with equal allocation to 4 treatment groups: 1. Resistance training (RT) (8 months, 3dwk-1) and placebo (PL) – Group = RT + PL; 2. RT as in # 1 + CrM (5 gd-1) and CLA (3 gd-1) supplementation– Group = RT+SUPP; 3. Sedentary (8 months of home stretching (SED)) and placebo (PL) = SED; 4. SED as in # 3 + SUPP as in # 2 – Group = SED+SUPP. *3. Major outcome variables.*A. Function – muscle strength (isometric and dynamic), aerobic capacity, functional tasks; B. Anthropometry – DEXA for fat-free mass, bone mineral content and density; C. Muscle – Histology – ATPase for fiber area and type, cytochrome oxidase (COX) negative fibers, COX sub-unit II and IV and 8-OH-2deoxyguanosine by IHC; Biochemistry – electron transport activity, creatine, ATP, phosphocreatine, protein carbonyls and anti-oxidant enzymes; Molecular biology – mitochondrial DNA deletions, gene expression pattern by micro-chip technology; D. Blood – CK activity, liver and renal function tests, bone turnover markers (osteocalcin and N-telopeptide); E. Urine - 8-OH-2deoxyguanosine/creatinine.

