  2. In our pilot study we had a drop-out rate of 7 %, and if we assume a drop-out rate of twice this (~ 6/group), we should retain 34 people at each of the two centers with 34 in RT and 34 on the combined supplement.

1. Design/Methodology:

Participants who are deemed eligible to participate will be randomly allocated into one of four groups. The allocation will be based upon an expected equal recruitment at the London (total = 40) and Hamilton (total = 40) sites and there will be 10 independent blocks of 4 randomly distributed interventions at each site (20 allocated to strength exercise (10 = + supplement; 10 = no supplement) and 20 allocated to no exercise (10 = + supplement; 10 = no supplement)) with an equal distribution:

1. Resistance training (RT) (12 months, 3dwk-1) and placebo (PL) – Group = RT + PL.

2. RT as in # 1 + CrM (5 gd-1) and CLA (3 gd-1) supplementation (SUPP) – Group = RT+SUPP.

3. Sedentary (12 months of home stretching (SED)) and placebo (PL) = SED.

4. SED as in # 3 + SUPP as in # 2 – Group = SED+SUPP.

1. Setting (e.g. outpatient, ICU, community):

The participants will be healthy ambulatory community dwelling men and women over the age of 65 y.

a. Exercise testing – Rm 4U18 and 2F MUMC (Neuromuscular research testing area – [name]).

b. Exercise training – Tue and Thur. – Ivor Wynne Center exercise center.

1. (a) Brief description of participants:

Men and women over the age of 65 y and less than 85 y who are living independently in the community with no contra-indications to exercise testing or training will be recruited.

(b) Are there any age, ethnicity, language, gender or race-related inclusion or exclusion criteria? [ ] YES [ X ] NO

If YES, please justify:

We plan to recruit equal numbers of men and women.

1. Study interventions:

a) Exercise training (50 % of recruits; other 50 % will continue with their usual routine) – participants will perform supervised strength/resistance exercise three times a week (Tue/Thur) for **12 months** using a machine based whole body exercise program that we have shown previously to be safe and effective (Brose, et al.,  *J Gerontol A Biol Sci Med Sci.*, 58:B11-9, 2003). Subjects will also perform a home based exercise routine on Saturday with rubber bands and resistance exercises not requiring weights (i.e., sit-ups).

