**SECTION D – PLAN FOR OBTAINING INFORMED CONSENT**

***Please complete the attached “Informed Consent Checklist” prior to completing this section.***

1. Describe how participants are to be recruited; if using advertisements include a sample with date.

Subjects will be recruited through advertisements around McMaster Campus, at local grocery stores and community centers and via a brief television appearance on the local Cable TV network in Hamilton (This was used successfully in an earlier training study in the elderly and more than twice the required subjects were recruited within a week).

1. Describe the relationship between the investigator(s) and the participant(s). Who will obtain consent?

Subjects will be not likely be known by any of the primary investigators. Informed consent will be obtained by either the study coordinator or one of the primary investigators.

1. Are participants competent to consent? [X ] YES [ ] NO If NO, describe the alternate source of consent.

If a minor, describe the procedure to be used. Where applicable, describe how you will obtain assent.

1. How will you assure ongoing consent from research participants?

The exercising participants will be required to come to the exercise training center twice a week (50 %). We will assume that their voluntary participation will indicate a willingness to continue in the study. There will be a mid-study (6 months) testing session where all aspects of the study will be reviewed. For the 50 % of participants who are not exercise training, they will come in for a 30 minute stretching session and to review any questions that arise.

1. What procedures will be followed for participants who wish to withdraw, either during or after the study?

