Subjects who withdraw prior to randomization or within the first week (i.e., before the first testing session) will not be considered to have started the study and will be thanked for their interest. There are a few individuals who may use the study as a vehicle to obtain free exercise training and may drop out if they are not randomized to the exercise group. In our experience, this is about 5 – 10 % of all persons and we will notify people whether they are in the exercise groups or not before the first testing session. Once in the study (i.e., after the first testing session) all drop-outs will be considered in an intention to treat analysis of the data and the reason for the withdrawal will be noted and will be part of the final manuscript. Participants who experience any side effect from the study (i.e., tendonitis from exercise training) will be covered for the costs of treatment (such as physiotherapy or anti-inflammatories) and if they drop-out because of a negative consequence of the study, they will be given the full remuneration.

1. Will you be contacting participants either by telephone or letter during the project? [X] YES [ ] NO

If YES, append a copy of the telephone script or list of questions with the research protocol.

Participants will be contacted by telephone to book times for their testing sessions in order to fit into their schedule.

“Hello, this is ____________ calling from the older adult training study. We would like to plan the times for your testing sessions. We have a number of open testing sessions available including, ………… dates. If none of these times is convenient for you, are there times that would be more appropriate for you? Do you know how to get to the McMaster Medical Center, if not, we can send you a map or explain it over the phone. Thank you for participating in the study and we look forward to seeing you on (time and date).”

If participants miss more than one exercise session, they will be contacted to see if there is anything wrong (i.e., are they ill, injured, still interested in participating?).

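### Fixed blocks of 4 within site, with exercise status disclosed, could let a recruiter who tracks allocations know one third of exercise assignments in advance

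*Protocol*

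**What the plan says.** The Research Plan in the protocol summary describes a "Randomized, double-blind study with equal allocation to 4 treatment groups". Section B, Part II, Design/Methodology gives the mechanism: "there will be 10 independent blocks of 4 randomly distributed interventions at each site", based on "expected equal recruitment at the London (total = 40) and Hamilton (total = 40) sites". The per-site totals are "20 allocated to strength exercise (10 = + supplement; 10 = no supplement") and "20 allocated to no exercise (10 = + supplement; 10 = no supplement"). Site is the only stratum named.

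Two statements in Section D bear on who can see what. On withdrawals: "we will notify people whether they are in the exercise groups or not before the first testing session". On consent: "Informed consent will be obtained by either the study coordinator or one of the primary investigators". Section C adds that the research coordinator screens candidates. The text available does not say who holds the list, whether recruiters are kept unaware of the block size, or when each allocation is released.

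On sex, the participant description says only: "We plan to recruit equal numbers of men and women".

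**The concern.** A short block of fixed, published size becomes predictable once one of its factors is visible. Here the supplement is blinded but exercise is not. Someone who has seen the first exercise assignments in a block can often deduce the rest, and the last place is always known.

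If that person also screens or takes consent, knowledge of the next assignment can affect who is entered and when. Several features of the protocol make this more than theoretical:

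- Some exclusions in Section C call for judgement and relate directly to exercise, such as a joint problem that would prevent strength training or a stress-test abnormality judged to make exercise risky.
- Section D expects 5 to 10% of people to leave if they are not given exercise, which gives staff a reason to steer keen candidates.
- People who leave before the first testing session are not counted as having started. The intention-to-treat rule covers only later drop-outs, so it cannot repair selection at entry.
- Strength, functional tasks and aerobic power depend on fitness and motivation, on which selected groups would differ.

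At stake is the comparability of the exercise and no-exercise groups at baseline. The protocol itself fixes the block scheme, and allocation has to be settled before enrolment, so this is not a detail left to an analysis plan.

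**Working it through.** **Inputs.** Block size 4, 10 blocks per site, two sites of 40, four arms in equal numbers (Section B, Part II). Exercise status open, supplement blinded (Section D; Research Plan).

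**The plan's own counts.** 10 × 4 = 40 per site; 2 × 40 = 80 in total; 10 per arm per site, 20 per arm overall. These reproduce. Each block has one place per arm, hence two exercise (E) and two no-exercise (N) places.

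**Assignments determined in advance.** The 24 orders of four arms collapse to six equally likely E/N patterns. A place is determined when all places left in the block have the same exercise status.

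- EENN and NNEE (2 of 6): the 3rd and 4th places are determined.
- ENEN, ENNE, NEEN and NENE (4 of 6): only the 4th is determined.

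Mean = (2×2 + 4×1)/6 = 1.333 of 4 = 33.3%. Over the trial, 80 × 1/3 ≈ 27 participants.

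**Best-guess accuracy.** The recruiter always guesses the status with more places left.

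| Place | Chance of a correct guess |
|---|---|
| 1st | 1/2 |
| 2nd | 2/3 |
| 3rd | (1/3)×1 + (2/3)×(1/2) = 2/3 |
| 4th | 1 |

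Mean = (0.500 + 0.667 + 0.667 + 1.000)/4 = 70.8%. A sequence that cannot be predicted gives 50%.

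**With larger and mixed blocks.** The same enumeration for a block of 8 gives 1.6 of 8 places determined (20.0%) and 66.6% best-guess accuracy. An 8+8+4 run fills 20 places, and two such runs fill a site.

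- Order of blocks known: (1.6 + 1.6 + 1.333)/20 = 4.533/20 = 22.7% determined.
- Sizes known but not their order (three equally likely orders, updated as assignments are seen): about 14% determined.
- Best-guess accuracy is about 67% in both cases.

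Mixing sizes therefore cuts certainty substantially but guessing only modestly, from 71% to about 67%. The rest of the protection has to come from keeping the block structure from recruiters.

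**Supplement.** Seeing exercise status alone does not reveal which of the two exercise places in a block carries the supplement, so supplement status is not determined while the blind holds.

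**The case against.** The strongest reply is that 33% is a ceiling, not an expected outcome. It needs a recruiter who knows the block size, knows where blocks begin and sees every earlier exercise assignment at the site before approaching the next candidate. The protocol does not say that recruiters have this information. If participants are allocated in batches, there is little to guess sequentially. An earlier training study recruited more than twice its target within a week, which makes batches conceivable, though it equally means a pool from which to choose. Explicit eligibility limits and contact with the family doctor also reduce discretion over who enters, though not over timing. All of this stands as a condition on the figure. It does not remove the weakness: the block size is printed, the investigators who may take consent can be expected to know it, and nothing in the available text conceals it.

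A second reply is that the lead question and both worked sample sizes concern the supplement, which is blinded, while the exercise contrast is said to need fewer than 10 per group. That rightly limits the point to the exercise comparison. But a small required sample does not protect against selection bias, and exercise effects are among the stated hypotheses.

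Two stronger readings are tempting and not supported:

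- A reader might infer that the scheme leaves the sexes unbalanced. It does not. With equal recruitment, each arm of 20 expects 10 men (SD about 1.9, assuming 20 men and 20 women per site in random order). A chance split of 13:7 or worse in at least one of the four arms is fairly likely (52%), but 25:15 or worse between exercise and no exercise occurs in only about 4% of randomisations. Chance imbalance does not bias a randomised comparison. The planning figures are changes in fat-free mass and strength, and nothing in the protocol shows that change differs by sex. Stratifying by sex is optional.
- A reader might infer that supplement assignments are also exposed, because unmasking one exercise participant would reveal the other in the same block. That presupposes a broken blind and known block membership, neither of which the protocol suggests.

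**Conclusion.** The point holds for exercise status only, and conditionally. For a recruiter who knows the block size and tracks earlier allocations at the site, 33% of exercise assignments (about 27 of 80) are determined in advance and 71% can be guessed. The arithmetic is exact under those conditions. Whether they would be met cannot be settled from the document, which neither describes concealment nor rules it out. The consequence is a risk of selection at entry into the exercise versus no-exercise comparison, not a demonstrated bias. The supplement comparison within exercise status is unaffected while its blind holds, and sex balance is left to chance, not disturbed. Because a better scheme is available at little cost before enrolment, the change is worth making.

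**What to change.** Before first enrolment, replace the stated scheme with three linked changes:

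1. Generate the list centrally, with block sizes of 4 and 8 varied at random within site.
2. Keep block sizes and their order out of every document the sites see, including the protocol text that now prints the block size.
3. Release each allocation only after the participant has been confirmed eligible and has consented.

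Equal allocation is kept when all blocks are completed: 40 places per site can be filled exactly with blocks of 4 and 8.

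The cost is a new list and a small edit to the protocol. An unfinished block of 8 could leave arms off by one or two. The third change also needs a check on timing. The protocol tells people their exercise status before the first testing session and does not say whether the tests that bear on eligibility (stress test, DEXA) belong to that session. If they do, disclosure would have to follow them, and some people who want only exercise would be tested before they leave.

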**SECTION B – DESCRIPTION OF PROPOSED RESEARCH**

**PART I: BRIEF SUMMARY (4 – 5 lines) OF PROPOSED RESEARCH WRITTEN IN SIMPLE ENGLISH APPROPRIATE FOR LAY REVIEWERS (Do not use jargon or medical short forms). USE THE FOLLOWING HEADINGS;**

**(i) Main Research Question(s)** – Do the dietary supplements creatine monohydrate and conjugated linoleic acid enhance the benefits of strength exercise training in older adults and do they increase muscle function, mass and bone density on their own?

**(ii) Why is this research important? –** Muscle weakness and bone loss are major causes of disability in older adults and strategies that enhance muscle and bone mass should have significant beneficial effects on health and mobility of older adults.

**(iii) What is being studied? –** Muscle strength, aerobic fitness, bone mass, functional capacity will be determined before and after one year of supervised weight training in older adults as compared to a cohort of adults who do not exercise. Within each group, half will be taking the dietary supplements, creatine monohydrate and conjugated linoleic acid.

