- Creatine has been used by millions of athletes throughout the world for over 5 years. There is one report of an individual with pre-existing renal disease who showed an apparent worsening of kidney function while supplementing and another report of interstitial nephritis in a young man taking twice the recommended maximal dose for 1 month. Because of these case reports we will be conservative and exclude those with known or the potential for (i.e., diabetes) kidney disease. There have been 2 longitudinal studies using creatine for > 1 month and neither has shown any significant adverse effects. All blinded trials that have measured renal function have not shown any deterioration. There have been some anecdotal reports of stomach cramps, however, this appears to be related to the consumption of un-dissolved powder in a minority of subjects. There have been 3 prospective trials in older adults (> 65y) with exercise training and creatine interventions with no reported side effects. We found no evidence of subjective side effects nor alterations in renal and hepatic function in our 4 month trial in older adults (Brose, et al.,  *J Gerontol A Biol Sci Med Sci.*, 58:B11-9, 2003).
- CLA. There have been no reports of adverse effects from CLA in any human studies and it is important to note that CLA is an essential fatty acid found naturally in products such as milk (Blankson, et al, ). The amount of fat from the CLA is about 5 % of the total dietary fat intake.
- Muscle biopsy. A muscle biopsy will be taken before and after the training from the *Vastus lateralis* (outer leg) muscle. [name] has performed over 10,000 of these in patients and healthy control subjects ranging in age from 1 week to 90 y. with the following complications:
- 4/10,000 with a local skin infection.
- 6/10,000 with a fibrous lump at the site of biopsy (connective tissue); all disappeared with massage after < 1 week.
- 4/10,000 with a small patch of numbness just past the biopsy incision (size of a quarter) due to cutting a small sensory nerve branch. In all cases complete recovery occurred in < 3 months.
- The muscle usually has a dull ache for 24-48 h (markedly reduced with ice and mild analgesics such as Tylenol or Advil).

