- In theory, one could damage a small motor branch of the m. *Vastus lateralis* and partially weaken the lower aspect of the muscle. This should not affect function for this muscle is only one of the four that have a role in knee extension. However, it has not been observed in any of the patients biopsied by [name].
- DEXA Scan: A DEXA scan is the most accurate measurement of body fat mass currently available. It uses a very low intensity radioactive beam to measure the amount of muscle and fat. The amount of radiation exposure is less than a cross-Canada airplane flight and much less than a standard chest X-ray (> 10 X less). There are no known risks with this test.
- Blood sampling. A single needle stick (Venipuncture) will be used to take blood three times during the study (pre-, mid- and post-test). The possibility of a small bruise at the site exists. The total amount of blood taken at any time is going to be 15 ml, which should have no negative effects.
- Muscle Testing/Training: Muscle strength testing may pose some risk for ligamentous or tendon injury. Knee extension strength is a standard testing and training method used in the elderly. In the last study that we completed in older adults (N = 28), there were no reported injuries from the testing or training. There are a number of these persons still participating in the “Seniors Exercise Program”.
- Exercise stress testing. We will not allow participants with abnormal resting ECGs or a blood pressure of > 160 mmHg systolic and/or 95 mm Hg diastolic to complete the exercise protocol (Bruce). It has been determined that the risk of a cardiac event during such testing is about 1/100,000. Subjects will feel tired at the end of the study and possibly light headed.

1. How will you manage and minimize the risks?

- Muscle Testing/Training: The training program that we have devised (see also Brose, et al.,  *J Gerontol A Biol Sci Med Sci.*, 58:B11-9, 2003), starts with low weights and gradually progresses as the individual adapts to the program. There is a light warm-up before each testing and training session. Any reports of tendon/ligament pain will be assessed by one of the supervising physicians and appropriate external consultation sought if it does not resolve with minor interventions.

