- Serum CK activity, bilirubin, gamma-glutamyl transferase (GGT), and creatinine will be taken pre-, at 6 months, and at the end of the study. The pre- and + 6 month values will be provided to two local staff physicians (gastroenterologist and cardiologist) who will review the data and determine if there are any alterations that require further investigation or withdrawl from the study.
- Exercise stress testing. Prior to starting the study, each participant will have a symptom limited exercise stress test completed to determine maximal oxygen consumption and to determine if there are any ECG abnormalities. Any abnormalities that are deemed to be a risk to participation in an exercise program will be used as an exclusion criteria and the family doctor will be provided with the test results for appropriate action. [name] will review the pre-study and + 6 month tests for study exclusion or study withdrawal at the 6 month testing period. A defibrillator will be on hand at the time of the testing and each subject will have a 12 lead ECG.
- General health risk. Each participant will complete a health questionnaire and will be screened by the research coordinator to ensure that there are no contra-indications to participation. The family doctor of each potential candidate will be contacted to determine whether there are any contra-indications to participation. Specific exclusion criteria will include: known coronary artery disease, congestive heart failure, renal failure, diabetes requiring insulin or > 5 mg Glyburide or equivalent, renal failure (creatinine > 120, potassium > 5.00 mmol/L), previous stroke, uncontrolled hypertension or hypertension requiring more than mono-pharmacotherapy, inability to consent due to cognitive difficulties, chronic obstructive pulmonary disease (FVC or FEV1 < 85 % of age predicted mean value or requiring any medication other than a puffer as needed) or joint related problem that would exclude them from performing the strength training. Furthermore, we shall exclude persons who have a hip or lumber spine bone mineral density that is > 2 SD below the age adjusted mean values (based upon the DEXA scan).

1. (a) Will participants be reimbursed for expenses? [X] YES [ ] NO

If YES, please provide amount(s) and item(s) covered.

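### The entry criteria and control instruction do not secure the non-exercising, unsupplemented comparators that the study question assumes

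*Protocol*

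**What the plan says.** The lay summary (Protocol, Section B Part I, item iii) describes a year of supervised weight training "as compared to a cohort of adults who do not exercise". Part II, Design/Methodology, labels arms 3 and 4 as sedentary with home stretching. Half of each exercise stratum receives placebo.

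Part II, Brief description of participants, sets the entry rule: men and women over 65 and under 85 "living independently in the community with no contra-indications to exercise testing or training will be recruited". Part II, Study interventions (a), says of the half not assigned to training that the "other 50 % will continue with their usual routine".

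The exclusions are in Section C, under the management of risks (general health risk). The list opens "Specific exclusion criteria will include: known coronary artery disease, congestive heart failure, renal failure, diabetes requiring insulin" and goes on through stroke, hypertension, cognition, lung disease and joint problems. It ends with low bone density: "we shall exclude persons who have a hip or lumber spine bone mineral density that is > 2 SD below the age adjusted mean values". The health questionnaire and coordinator screening described there look for contra-indications. No section shown names current or recent resistance training, or use of creatine or CLA, as a reason for exclusion. None sets a washout or restricts these supplements outside the study.

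**The concern.** The comparator is defined in one place and not enforced in another. For someone who already lifts weights, keeping to a usual routine means continuing to lift weights, yet that person would be analysed as sedentary. Likewise, someone taking creatine on their own account could be randomised to placebo and continue taking it.

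Randomisation spreads such people evenly over the arms, so this is not confounding. The risk is attenuation. A participant whose outcome is much the same under either assignment adds to the sample size but not to the difference. Interpretation also suffers, because the result would no longer be the stated contrast with people who do not exercise, and a null finding could not be told apart from a mixed comparator. Later analysis cannot fully repair who was enrolled, so the matter belongs in the protocol.

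**Working it through.** **1. The plan's own figures.** Part II, Sample size, uses n/group = 2[(Zα + Zβ)·SD/δ]² with 1.96 and 1.28.
- Fat-free mass (δ 1.39 kg, SD 0.68): 2[(3.24 × 0.68)/1.39]² = 5.0. The plan states 10.
- Knee extension (δ 28 Nm, SD entered as 20): 2[(3.24 × 20)/28]² = 10.7. The plan states 21.

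The stated values match twice the formula (10.05 and 21.4). That is a separate matter. The check below uses the plan's δ and SDs and its expected retention, and does not use these n values.

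**2. Inputs.**
- Retention: 20 per cell × 0.86 ≈ 17; the plan gives 34 per factor level.
- Knee extension: 52 − 24 = 28 Nm. The arm SDs are 38 and 13. Their mean is 25.5 (the plan's figure) and their root mean square is √[(38² + 13²)/2] = 28.4.
- Fat-free mass: 1.92 − 0.53 = 1.39 kg. The root-mean-square SD is √[(0.98² + 0.38²)/2] = 0.74.
- c, the share gaining nothing more from assignment, is **not in the documents**. Values from 0 to 30% are assumed, with the SD left unchanged.

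**3. Where the factor (1 − c) comes from.**
- *Supplement contrast.* Suppose a prior creatine user who starts training gains 52 Nm whichever capsule is assigned. At c = 10%, RT + PL averages 0.9 × 24 + 0.1 × 52 = 26.8, and the difference is 52 − 26.8 = 25.2 = 0.9 × 28.
- *Training contrast.* Outcomes are measured at baseline, 6 and 12 months. A stable habitual trainer changes little in SED, much as a sedentary control does, and gains little in RT. The loss therefore arises mainly in the RT arm, and it is again a factor (1 − c).

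**4. Power for knee extension.** Two-sided t-test at 0.05, non-centrality λ = 28(1 − c)/[SD·√(2/n)]. For n = 17 and SD 25.5, λ is 3.20, 2.88 and 2.56 at c = 0, 10 and 20%. For SD 28.4 it is 2.87, 2.59 and 2.30.

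| c | δ (Nm) | 17 per cell, SD 25.5 | 17 per cell, SD 28.4 | 34 per level, SD 25.5 | 34 per level, SD 28.4 |
|---|---|---|---|---|---|
| 0 | 28.0 | 87% | 80% | 99% | 98% |
| 10% | 25.2 | 80% | 71% | 98% | 95% |
| 20% | 22.4 | 70% | 61% | 95% | 89% |

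The 17-per-cell columns are RT+SUPP against RT+PL, which addresses the first main question, whether the supplements enhance training.

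**5. Fat-free mass.** The difference becomes 1.39 × 0.90 = 1.25 kg or 1.39 × 0.80 = 1.11 kg. Even at c = 30% (0.97 kg), power at 17 per cell is about 96% with SD 0.74.

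**6. Training against sedentary.** The plan says almost every variable needed fewer than 10 per group. Required n rises by 1/(1 − c)², which is 1.56 at c = 20%. That gives fewer than 10 × 1.56 = 15.6, still below 17 per cell and 34 per level. If that statement is right, what is at stake for the training contrast is the size and meaning of the estimate more than its power.

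**The case against.** The strongest reply is that the intent is clear and the document is a short ethics form. The entry sentence is a brief description, and the exclusion list answers a question about managing risk, so a medical list is natural there. It is introduced as what the criteria will include, which need not be exhaustive. Controls are called sedentary, attend stretching sessions every two weeks, and are offered help to start exercising afterwards. All of this presumes that they do not already train.

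Much of this stands. A reader might infer that a site must accept a habitual trainer or creatine user; the text does not oblige that. It only gives no written ground for refusal, and the usual-routine instruction still conflicts with the stated comparator.

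A reader might also infer that the local pool is known to be contaminated. The documents do not show it. Section C says of the earlier study's 28 participants, "There are a number of these persons still participating in the" seniors' exercise programme. Section D, however, expects recruits mostly to be unknown to the investigators, and nothing is said about such a programme in London. Section C also says "Creatine has been used by millions of athletes throughout the world for over 5 years", but that concerns athletes, not community-dwelling adults over 65. No passage reports CLA use in this population.

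Finally, baseline strength, the nutritional assessment and muscle creatine from the biopsies would make some prior exposure visible. None of these is tied to eligibility.

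**Conclusion.** The point holds as a gap between the stated comparator and the rules meant to produce it. The training and supplement effects *can* be diluted. A reader might go further and conclude that they *are*, or that the training effect shrinks from both sides. The documents give no prevalence, and under a change-from-baseline outcome a stable trainer in SED behaves much like a sedentary control.

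The case is stronger for prior training, where a written instruction contradicts the comparator, than for supplement use, where it rests on silence. The material power loss is confined to knee extension at about 17 per cell: 7 to 9 percentage points at c = 10% and 17 to 19 at c = 20%. Fat-free mass and the pooled comparisons have room to absorb it.

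These figures assume that an affected participant gains nothing further, which is an upper bound: a prior creatine user could still respond to CLA, and a habitual trainer to the supplement. Applying c to the RT+SUPP against RT+PL contrast means counting prior supplement users, plus any habitual trainers in whom the supplement adds nothing. This is a worthwhile, inexpensive improvement, not a fatal flaw.

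**What to change.** - Add to the Section C exclusions regular resistance training, and use of creatine or CLA supplements, each within a look-back period that the sponsor fixes before enrolment. Screen with the health questionnaire already planned.
- In Section B Part II, Study interventions, reconcile the usual-routine instruction with the non-exercising comparator: ask SED participants not to start resistance training during the study, and ask all participants not to take creatine or CLA outside it.
- Record both exposures at the 6- and 12-month visits, so that any remaining dilution can be described.

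The cost is a short amendment and a few extra questions. The downside is slightly narrower eligibility and possibly slower recruitment. Section D reports that an earlier training study drew more than twice the required number within a week, which suggests that the Hamilton site at least could bear it.
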